## Methods/design

### Aims

The primary aim of this study is to determine the prevalence, type, and severity of CHC in survivors of DS-AL and to compare CHC outcomes to those of frequency-matched individuals with DS with no cancer history. Secondary aims include characterizing post-treatment clinical outcomes of DS-AL, determining prevalence and severity of parent-reported neurocognitive outcomes in survivors of DS-AL compared with frequency-matched individuals with DS without leukemia, determining health-related quality of life in survivors of DS-AL, and identifying clinical risk determinants of CHC, neurocognitive outcomes, and clinical outcomes in survivors of DS-AL. Biological and molecular correlations will be tested in exploratory aims, i.e., we will test whether structural birth defects and genetic alterations associated with etiology also demonstrate associations with CHC in DS-ALL, and whether telomere length is associated with in-person-assessed neurocognitive outcomes in DS-ALL.

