**Fig. 1 Fig1:**
[figure not shown]
Study Design Schema for COG ALTE22C1. ^See Table 1 for list of measures

Part 1 is conducted remotely through REDCap® [16, 17] (with a paper alternative) and consists of a medical record release, medical condition survey (completed by parent proxy and verified by medical record review), and saliva sample. Part 1 also includes a neurocognitive battery completed by parent proxy and designed to evaluate executive function and self-regulation, social competence, problem behaviors, autism spectrum behavior, communication, adaptive behavior, and quality of life. The measures included and their target area of assessment are shown in Table 1 [18–23]. Part 2 is focused on in-person assessments and requires local COG site activation of this central-IRB-approved protocol. For Part 2, consent is obtained by COG site personnel. Resources are available to sites that support inclusion in research of persons with intellectual disabilities [24], including a visual break board for survivors to direct the pace of the consent conversation and request a pause or stop if needed (Fig. 2) [25]. Part 2 comprises an in-person, COG Long-Term Follow-Up Guidelines [26]-informed and Down Syndrome Guidelines [27, 28]-informed long-term follow-up visit. Results of the clinic visit, including diagnosis and treatment information, complete review of systems, vital signs and anthropometrics, Tanner staging, list of medication, and results of any laboratory or diagnostic tests, are reported by the COG site-based research team via REDCap® to the central data coordinating center. Part 3 comprises a comprehensive, in-person neurocognitive evaluation on a subset of ALL survivors and research blood draw, also requiring COG site activation in addition to COG site-based training. The COG site-based research team administers the NIH Toolbox Cognitive Battery (NIH-CB) using a study-supplied tablet. The NIH-CB is validated in persons with intellectual disability [29, 30] and includes seven tests: Flanker Inhibitory Control and Attention, Dimensional Card Sort, List Sorting Working Memory, Oral Reading Recognition, Pattern Comparison Processing Speed, Picture Sequence Memory, and Picture Vocabulary. The Part 3 required research blood draw is banked for future assessment of leukocyte telomere length by telomere flow-fluorescence in situ hybridization (FISH) [31].

**Table 1 Tab1:** Part 1 and Part 3 Neurocognitive Measures Included in COG ALTE22C1

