For Part 3, we will use Cox regression to estimate the HR and 95% CI for number, severity, and type of CHC, as well as for neurocognitive deficits dichotomized as clinically significant impairment yes/no (≤ 1.5 SD outside of the mean for the age-normative sample) according to age at diagnosis, years off therapy, sex, race/ethnicity, diagnosis, and treatment exposures. We will use Cox regression to estimate HR and 95% CI for number, severity, and type of CHC by number of birth defects, as well as explore the role of DS-ALL susceptibility variants identified in our genome-wide assessment [46] on DS-associated CHC in survivors. All models will be adjusted for sex, genetic ancestry (estimated using the top 10 principal components), and age at diagnosis (years). We will determine genetically-estimated telomere length (TL) using methods described previously [47] and use a multivariable Cox proportional hazard model to estimate HR, 95% CI for the association between each of nine variants and risk for neurocognitive deficit ≤ 1 SD below the mean, considering the weighted and unweighted risk score from the number of risk alleles present and previously-published beta estimates. For flow-FISH analyses, TL ≤ 1 st percentile is considered ‘very short,’ as previously defined [48]. We will determine ORs for neurocognitive deficits ≤ 1.5 SD below the mean for a DS age-normative sample in subjects with TL > or ≤ 1 st percentile, adjusted for relevant covariates and treatment factors (e.g. ALL, AML). We will report 95% CI, p values using McNemar’s test (two-tailed p-value of 0.05 statistically significant).

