### Study progress

ALTE22C1 opened for recruitment in June 2023. As of August 2025, 55 COG sites have activated the protocol and 112 participants have been enrolled to Part 1, 73 to Part 2, and 6 to Part 3.

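### The risk-determinant models are labelled as Part 3, an ALL-only subset, although the secondary aim they serve covers all DS-AL survivors and the models include diagnosis as a term

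*Protocol article*

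**What the plan says.** Four places in the protocol article bear on this.

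- **Aims.** One secondary aim is "identifying clinical risk determinants of CHC, neurocognitive outcomes, and clinical outcomes in survivors of DS-AL". DS-AL covers ALL and AML: eligibility admits both, and the sample size section plans 200 DS-ALL and 100 DS-AML survivors.
- **Study design (text after Fig. 1).** "Part 3 comprises a comprehensive, in-person neurocognitive evaluation on a subset of ALL survivors and research blood draw". Part 3 adds the NIH Toolbox battery and the blood sample banked for flow-FISH telomere length. The medical conditions survey with record review, the caregiver-completed battery and the saliva sample all belong to Part 1.
- **Statistical analyses, last paragraph.** "For Part 3, we will use Cox regression to estimate the HR and 95% CI for number, severity, and type of CHC", together with dichotomized neurocognitive deficit, "according to age at diagnosis, years off therapy, sex, race/ethnicity, diagnosis, and treatment exposures". The birth-defect and susceptibility-variant models follow in the same paragraph. So does the flow-FISH analysis, which is "adjusted for relevant covariates and treatment factors (e.g. ALL, AML").
- **Study progress.** As of August 2025, "112 participants have been enrolled to Part 1, 73 to Part 2, and 6 to Part 3".

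**The concern.** The Statistical analyses section is organised by study part: Part 1 CHC data, Part 1 neurocognitive data, Part 2, Part 3. An analyst would therefore take the opening words of the last paragraph as naming the data set. On that reading, an aim about all DS-AL survivors is answered in a subset of ALL survivors who had in-person testing and a blood draw. A predictor the plan asks for does not vary there. Survivors who already have the relevant outcome data are left out. At stake are the scope and precision of one secondary aim: which exposures and patient characteristics predict late effects among survivors, including AML survivors and AML-type treatment exposures.

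**Working it through.** The article gives no sample size or power for Part 3 or for the determinant models, so there is no stated figure to reproduce. The check sets the passages side by side and then illustrates scale.

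**Step 1. Does the model fit its stated population?**

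| Element | Required by | Available in Part 3 as defined |
|---|---|---|
| ALL and AML survivors | Aims (DS-AL) | ALL only |
| Diagnosis as predictor | Determinant model | Constant; coefficient not identifiable |
| ALL/AML as adjustment factor | Flow-FISH analysis | Constant; blood draw is a Part 3 item |
| CHC with onset date | Determinant and birth-defect models | Collected in Part 1, so Part 3 is not needed |

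The neurocognitive outcome in the determinant model uses the same 1.5 SD impairment cut-off, against the age-normative sample, that the Part 1 neurocognitive paragraph uses for the caregiver ratings. That outcome also exists for Part 1 survivors.

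**Step 2. Do the Part 1 paragraphs supply the determinant models instead?** No. The Part 1 CHC models estimate the effect of ALL, AML or any AL diagnosis, with DS controls as the comparison, and cancer characteristics enter only as adjusters. The Part 1 neurocognitive paragraph compares scores and proportions between groups. Neither is stated as a model of determinants within survivors.

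**Step 3. Who is left out at the August 2025 count?**

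- In Part 3: 6/112 = 5.4% of Part 1.
- Outside the models on the literal reading: (112 − 6)/112 = 106/112 = 94.6%.
- The determinant sentence lists six predictors, so at least six parameters, against 6 participants.

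**Step 4. What does the analysis set do to precision?** This is a best case. It assumes that every participant has an event and that there is one binary determinant, with two-sided alpha 0.05 and 80% power. Schoenfeld's formula gives the minimum detectable HR = exp[(1.960 + 0.842)/√(E·p·(1−p))], where E is events and p the share with the factor.

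| Set | E | p | HR |
|---|---|---|---|
| Part 3 to date | 6 | 0.5 | exp(2.802/√1.5) ≈ 9.9 |
| Part 1 to date | 112 | 0.5 | exp(2.802/√28) ≈ 1.70 |
| Planned survivors (200 + 100) | 300 | 0.5 | exp(2.802/√75) ≈ 1.38 |
| Planned, ALL vs AML at 2:1 | 300 | 1/3 | exp(2.802/√66.7) ≈ 1.41 |
| ALL-only Part 3, ALL vs AML | any | 0 or 1 | not estimable |

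**Step 5. What if Part 3 grows?** The final Part 3 size is not stated, so these are assumed scenarios. For a determinant assessed among ALL survivors only, the standard error relative to the planned 200 grows by √(200/n). With n = 50 this is √4 = 2.0. With n = 16, which is 6/112 × 300 and assumes that the present ratio persists, it is √12.5 ≈ 3.5. The diagnosis effect stays inestimable in every scenario.

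**The case against.** The strongest reply is that the label is loose and the exclusion was never meant. The paragraph names diagnosis, and ALL and AML, which make no sense in an ALL-only set. It also analyses CHC and birth defects, which do not depend on Part 3. It reads like a heading under which a condensed article gathered its secondary and exploratory analyses. This is plausible, and it means that the text does not establish a decision to drop AML survivors. It does not remove the problem: if the label is a slip, the analysis set for a secondary aim is stated wrongly.

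A reader might go further and infer any of the following, which the article does not support:

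- *That the Part 1 data go largely unused.* They carry the CHC prevalence estimates, the pooled logistic and stratified Cox models, and the neurocognitive comparisons. The loss is confined to the models in this one paragraph.
- *That nothing will be learned about AML survivors.* AML is compared with DS controls in the Part 1 CHC models, DS-AL subgroups are compared with controls on the neurocognitive scores, and Part 2 results are compared between DS-ALL and DS-AML survivors.
- *That Part 3 will end with a handful of participants.* Six is an interim count. Part 3 needs site activation and site training, so its accrual need not track Part 1.
- *That the birth-defect and telomere analyses wrongly omit AML.* The Aims restrict both to DS-ALL; the telomere question, for example, is "whether telomere length is associated with in-person-assessed neurocognitive outcomes in DS-ALL". For the birth-defect models, only the restriction to the Part 3 subset is open to question.

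**Conclusion.** The concern holds as an internal contradiction limited to one secondary aim and to the birth-defect models placed beside it. The aim covers all DS-AL survivors, the determinant models are labelled Part 3, Part 3 is ALL-only, and the models contain a term that cannot vary there. That the ALL-versus-AML effect cannot be estimated follows from the definitions alone and needs no assumption about numbers. That all AML survivors and 94.6% of current Part 1 survivors fall outside these models follows only if the label is taken literally and at the August 2025 count. The detectable hazard ratios and standard-error factors are best-case or scenario figures that show direction and rough scale; they do not forecast the final analysis.

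**What to change.** Restate the analysis sets in the last paragraph of Statistical analyses:

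1. The clinical risk-determinant models for CHC and for caregiver-rated neurocognitive impairment use all Part 1 survivors, ALL and AML, with diagnosis kept as a predictor.
2. The birth-defect models use all Part 1 DS-ALL survivors, as the Aims specify.
3. The Part 3 label applies only to NIH Toolbox and flow-FISH outcomes.
4. The ALL/AML term is removed from any model confined to Part 3, including the flow-FISH analysis.

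The cost is wording. CHC with onset dates and the caregiver ratings are already Part 1 items for every survivor, so no new data collection is needed. The study is described as ongoing, so the change can be made before analysis.

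### Cox regression is specified for yes/no neurocognitive deficits that are observed at one assessment and have no event time

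*Protocol article*

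**What the plan says.** The Part 3 paragraph of Statistical analyses plans to "use Cox regression to estimate the HR and 95% CI for number, severity, and type of CHC, as well as for neurocognitive deficits". The deficit is "dichotomized as clinically significant impairment yes/no (≤ 1.5 SD outside of the mean for the age-normative sample", and the determinants are entered "according to age at diagnosis, years off therapy, sex, race/ethnicity, diagnosis, and treatment exposures". Later in the paragraph the plan is to "use a multivariable Cox proportional hazard model to estimate HR, 95% CI for the association between each of nine variants and risk for neurocognitive deficit", here with a cut-off of 1 SD below the mean. For telomere length measured by flow-FISH, the same paragraph changes to odds ratios: "We will determine ORs for neurocognitive deficits ≤ 1.5 SD below the mean for a DS age-normative sample".

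On the data themselves, Study design says that "Part 3 comprises a comprehensive, in-person neurocognitive evaluation on a subset of ALL survivors and research blood draw". The Part 1 parent-proxy battery is likewise described as completed once. The data collection section records dates of onset for chronic health conditions (CHC) and none for neurocognitive deficits. The censoring rule in Statistical analyses covers subjects without a CHC event. It mentions neurocognitive data only as one of the updates that close a control's follow-up.

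**The concern.** A Cox model needs, for each subject, a time at which the event occurred or a time up to which it had not. A deficit found at a single assessment supplies neither. A subject with a deficit acquired it at some unknown earlier age, or has always had it. The only time available is when the test took place, so the model describes when subjects with deficits were tested.

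This matters because enrollment runs from age 6 to under 40, so testing ages will differ widely. A determinant linked to testing age can appear harmful or protective when it is neither, and a real effect can disappear. The analyses affected are the neurocognitive part of the secondary aim on clinical risk determinants and one exploratory telomere analysis.

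**Working it through.** **Stated figure.** The article gives no sample size, power or expected result for these Part 3 models, so there is nothing to reproduce. Its power figures concern CHC hazards and mean scores.

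**What the model would estimate.** Let p1 and p0 be the deficit prevalences in exposed and unexposed subjects, and g1(t) and g0(t) the hazards of being tested at age t. Take age at testing as time, the deficit as event and no deficit as censoring. If the deficit is unrelated to testing age within each group, then

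HR(t) = (p1 / p0) × (g1(t) / g0(t)).

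The first factor is the prevalence ratio. The second concerns only when people were tested. It equals 1 if testing ages are balanced, and otherwise it distorts the result.

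**Simulation with no true effect.** Assumed, because the article does not give them: age at testing as time scale, n, prevalence and age gap.

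*Setting A:* n = 200, prevalence 40%, SD of testing age 6 years, exposed tested younger (15 against 18 years for the 3-year gap). Ranges are across repeat runs.

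| Gap | Cox HR | Cox rejection |
|---|---|---|
| 0 years | 1.01 | 4% |
| 3 years | 1.57 to 1.60 | 51% to 53% |
| 5 years | 2.13 to 2.19 | 89% to 93% |

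Logistic regression stayed at about 5% or below.

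*Setting B:* exposed tested later, 300 datasets per cell.

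| n | Prevalence | Gap | Median HR | Cox rejection | Logistic rejection |
|---|---|---|---|---|---|
| 100 | 30% | 3 years | 0.63 | 22% | 4% |
| 100 | 60% | 3 years | 0.65 | 36% | 6% |
| 200 | 30% | 3 years | 0.66 | 33% | 5% |
| 200 | 60% | 3 years | 0.66 | 62% | 6% |
| 200 | 60% | 6 years | 0.43 | 99% | 5% |

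With no gap, the median HR was 0.95 to 1.02 and rejection 3% to 7%. The two settings agree: 1/1.59 = 0.63, the same bias in the opposite direction. The size of the bias hardly depends on n; the false-positive rate does.

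**A true effect can vanish.** Take a true odds ratio of 2, prevalence 30% in the unexposed, n = 200, and exposed tested 3 years later. The unexposed odds are 0.30/0.70 = 0.429. Doubled they are 0.857, so p1 = 0.857/1.857 = 0.46 and p1/p0 = 1.54. Multiplying by the null HR of 0.66 predicts 1.54 × 0.66 = 1.02. The simulated Cox HR was 0.98, with 3.5% rejection. Logistic regression gave an odds ratio of 1.97 and rejected in 62%.

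**The listed determinants.** Age at testing = age at diagnosis + treatment duration + years off therapy. Two of these three terms are on the covariate list. With both entered, the Cox fit was usable in only 6 of 40 datasets. That run held treatment duration at 2.5 years, so the covariates almost fixed the time variable; real variation in duration would make the failure less complete.

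**Comparison within the plan.** The flow-FISH analysis treats the same kind of outcome as a prevalence outcome with odds ratios. Only the two Cox models depart from this.

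**The case against.** The strongest reply is that the article states no time scale for these models, so the figures above depend on a choice it does not make. That stands, and the figures are conditional on it. A Cox model with one constant time for everyone is a known device for prevalence ratios. At the same age gaps it gave HRs of 0.99 to 1.01. It rejected in at most 1% of datasets, however, so its standard errors are too large without correction, and the article neither states this device nor reports the result as a prevalence ratio. No choice of time scale supplies the missing onset.

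A second reply is that balanced testing ages give no bias under the null. That is true, and it largely protects the nine-variant model, since nothing in the article suggests that germline variants follow testing age. It cannot protect age at diagnosis or years off therapy, which are parts of testing age.

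A reader might also infer three stronger points that the document does not support:

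- *That number and severity of CHC have no event time.* CHC are abstracted with onset dates and graded, so time to a first CHC of a given grade, or to the k-th CHC, is a proper Cox outcome. What the article leaves open is which event is meant.
- *That the genetic and telomere results as a whole would be artefacts.* The susceptibility-variant and birth-defect models concern CHC, and the flow-FISH analysis uses odds ratios.
- *That diagnosis is a constant covariate because Part 3 testing covers ALL survivors only.* The same paragraph models CHC and names both ALL and AML as factors, so its label may simply be loose.

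**Conclusion.** The point holds for neurocognitive deficits, in both Cox models of the Part 3 paragraph. A status seen once has no observed event time, so a hazard ratio for it cannot be read as a hazard, whatever the time scale.

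The numerical bias is conditional. With age at testing as time, no true effect, n = 200 and 40% prevalence, a 3-year gap gives an HR of about 1.6 and about 50% false positives. The risk-determinant model is directly exposed. The nine-variant model would be biased only if the variants track testing age.

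The primary CHC comparison and the survivor-control comparisons of neurocognitive scores and proportions do not use these models and are unaffected.

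**What to change.** - Replace both Cox models for neurocognitive deficits with logistic regression (odds ratio) or modified Poisson regression (prevalence ratio), or with linear regression on the score. This brings them into line with the flow-FISH analysis.
- Adjust for age at testing. Do not enter it together with both age at diagnosis and years off therapy where these nearly determine it; state which of the three are used.
- Keep Cox for CHC, and define number and severity as time to a stated event, for example first CHC of a given grade or the k-th CHC.

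The cost is rewording one paragraph. No new data are needed, and with 6 participants in Part 3 as of August 2025 the change can be made well before analysis.

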### Recruitment, population, and eligibility

A unique feature of this observational survivorship trial is the hybrid recruitment approach that leverages the COG Childhood Cancer Research Network (ACCRN07) and Project EveryChild (APEC14B1) research registration and biobanking protocols [33, 34]. Potential participants with DS-AL are identified and recruited by two mechanisms run in parallel: 1) The Coordinating Center conducts centralized recruitment of patients that have consented to recontact and were enrolled to either ACCRN07, APEC14B1, and/or AEPI20N2 The DS-ALL Deep Phenotyping Project: Evaluating the Association Between Co-occurring Birth defects and ALL Risk in DS; 2) Site-based prospective recruitment at COG sites that have activated the study protocol (only for subjects not enrolled to any of the above registries or studies).

Eligible survivors are those with DS-AL who are ≥ 6 years old and < 40 years old, in remission, at least 36 months off primary cancer treatment, and able to understand either English or Spanish. Bone marrow transplant recipients are excluded (see Table 2). A diagnosis of Down syndrome is required and may include any of the three recognized types: trisomy 21 resulting from chromosomal nondisjunction (most common), translocation (the patient has 46 chromosomes, but all or part of an additional copy of chromosome 21 is attached to another chromosome), or mosaicism (trisomy 21 that is present in only a fraction of cells). All participants to ALTE22C1 must be a survivor of either ALL or AML/myeloid leukemia of DS (ML-DS) requiring treatment with chemotherapy and may not have had any other cancer diagnosis other than transient abnormal myelopoiesis. Based on the racial and ethnic distribution of childhood leukemia in the United States, the sample is expected to be 70% White, 10% Black, 20% other or multi-race, and about 20% Hispanic (estimates derived from the Surveillance Epidemiology and End Results Program).

**Table 2 Tab2:** Eligibility Criteria for COG ALTE22C1

Inclusion Criteria
• Age ≥ 6 and < 40 years at the time of enrollment
• Diagnosis of Down syndrome
• Survivor of ALL or AML treated with chemotherapy for their cancer diagnosis
• Completed treatment at least 36 calendar months prior to enrollment
• Life expectance > 1 year
• English or Spanish speaking
Exclusion Criteria
• History of hematopoietic stem cell transplant
• History of another cancer either prior to or subsequent to the ALL/AML diagnosis

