### Data collection, classification and handling of missing or incomplete data

Part 1 measure responses will be securely transmitted electronically after completion by parent proxy to a central study database or manually entered for any responses on paper. Part 1 CHC data, including date of onset, are abstracted, categorized by organ system, and graded using the CTCAE v5.0 at the Data Coordinating Center, using previously described methods for identifying CHC in childhood cancer survivors [42]. Part 1 neurocognitive data are scored at the Neuropsychology Coordinating Center, with final scores entered in REDCap. Part 2 clinical outcome results are securely transmitted electronically from the COG site to a central study database and categorized by the Data Coordinating Center as ‘normal’ or ‘abnormal.’ Any missing tests recommended by clinical practice guidelines are noted as ‘incomplete.’ The availability of in-home, remote completion, loaner tablets, and mobile Wi-Fi hotspots, in addition to compensation, are expected to facilitate data collection and reduce data missingness. Results from parent proxy neurocognitive assessments are summarized and provided to families at no cost to further incentivize participation and to facilitate subject access to special needs services.

For DS control participants, outcome data are collected using identical measures to assess CHC in addition to parent proxy completion of an identical neurocognitive battery. Similar to DS-AL cases, medical outcomes are verified by medical record review after a medical release is obtained, including both birth defects and CHC (type, severity, date of onset). DS controls do not complete the NIH Toolbox assessment and do not submit a biological specimen.

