### Statistical analyses

For Part 1 data, the prevalence for each CHC will be estimated and compared with published CHC prevalence and grading data from non-DS AL survivor cohorts using CTCAE criteria [10, 11, 43, 44]. We will then construct longitudinal data to power time-to-event analyses, using two modeling approaches [45] to account for time-varying independent variable (diagnosis with AL) effects on time to a dependent variable (CHC incidence and CHC-free survival). Subjects without a CHC event will be censored at the time of study enrollment (DS-AL) or update of CHC or neurocognitive data (DS controls). For all analyses, we will pool observations over equal length intervals of chronologic age to predict short term risk of CHC during each age interval. First, we will use pooled logistic regression to estimate OR, 95% CI, and p-values for association of ALL, AML, or any AL diagnosis with medical record-verified CHC, agnostic of time to CHC. Next, we will use stratified Cox models to refine associations of ALL, AML, or any AL diagnosis with CHC based on time to CHC incidence. Within each age interval, we will estimate the hazard ratios (HR), 95% CI, and p-values to report time-dependent effects of ALL, AML, or any AL diagnosis on CHC. All models will be adjusted for age, sex, race/ethnicity, and relevant cancer or DS characteristics.

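### Taken at enrollment, years off therapy is essentially potential follow-up time, so its Cox hazard ratio cannot show whether the risk of chronic health conditions rises with time off therapy

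*Protocol article*

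**What the plan says.** All references are to the protocol article.

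- **Aims** include "identifying clinical risk determinants of CHC, neurocognitive outcomes, and clinical outcomes in survivors of DS-AL", as a secondary aim.
- **Statistical analyses, Part 3 paragraph**, serves that aim: "we will use Cox regression to estimate the HR and 95% CI for number, severity, and type of CHC". The same sentence covers "neurocognitive deficits dichotomized as clinically significant impairment yes/no". The factors follow: "according to age at diagnosis, years off therapy, sex, race/ethnicity, diagnosis, and treatment exposures".
- **Statistical analyses, Part 1 paragraph**, sets the end of follow-up for survivors: "Subjects without a CHC event will be censored at the time of study enrollment (DS-AL". It also gives the only stated axis: "For all analyses, we will pool observations over equal length intervals of chronologic age".
- **Data collection** makes the CHC outcomes dated events: "Part 1 CHC data, including date of onset, are abstracted".
- **Eligibility (Table 2)** ties time off therapy to enrollment: "Completed treatment at least 36 calendar months prior to enrollment".

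The article states no time origin for the Part 3 Cox models. It does not say whether years off therapy is fixed at enrollment or updated over time.

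**The concern.** A Cox model compares people at the same moment on the clock. A covariate in it should describe what is true of them at that moment. Years off therapy at enrollment does not: a survivor who enrolls 15 years after treatment carries the value 15 throughout, including at year 1. For that person it says when observation stops. It does not say how long ago treatment ended at the time of risk.

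At stake is one factor under the risk-determinant aim. A hazard ratio near 1 could be reported as no association between CHC and time since treatment, although the model had no means of detecting one. A hazard ratio away from 1 could be read as late-emerging risk when it reflects treatment era or who chose to take part. The Discussion expects the results to inform survivorship care and surveillance, where either misreading could matter.

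**Working it through.** The plan gives no figure for this model. Its power figures concern survivors against controls and do not bear on the point.

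**Structure.** Let s be time since end of therapy, D age at diagnosis, L treatment duration, and Y years off therapy at enrollment. Age at enrollment is D + L + Y.

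1. *End-of-therapy clock.* Censoring occurs at s = Y, so Y is exactly the potential follow-up time. If enrollment timing is independent of CHC risk, the hazard at s is the same for every Y ≥ s. The coefficient of Y is then zero, and any rise with s goes into the baseline hazard.
2. *Age axis.* Censoring occurs at age D + L + Y. With D also in the model, as the plan lists, Y is the censoring age apart from L.
3. *Time-updated value, end-of-therapy clock.* It equals s for everyone at risk, so it cannot be estimated.
4. *Time-updated value, age axis.* At age a it is a − D − L. Age a is common to the risk set, so only D + L varies. With D in the model, only L remains to identify the effect.

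**Simulation.** From the plan: 200 DS-ALL + 100 DS-AML = 300 survivors, enrollment age 6 to under 40, and at least 3 years off therapy. Assumed, because the documents do not give them: age at diagnosis uniform from 1 to 10 years; treatment lasting 0.6 to 3 years; enrollment age uniform over the eligible range; Weibull hazard since end of therapy with 50% incidence at 20 years. The hazard at 20 against 5 years is (20/5)^(shape − 1), which is 4 for shape 2 and 16 for shape 3. Averaged on the log scale, this is 4^(10/15) = 2.5 and 16^(10/15) = 6.3 per 10 years.

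Median hazard ratio per 10 years off therapy, with the share of runs significant at 5% (60 to 150 runs per scenario):

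| Clock and coding | 4-fold rise | 16-fold rise |
|---|---|---|
| End of therapy, fixed, with age at diagnosis | 1.01–1.03 (5–7%) | 0.99–1.01 (3%) |
| Diagnosis, fixed, with age at diagnosis | 1.02 (5%) | 1.01 (3%) |
| Age, fixed, with age at diagnosis | 1.00–1.03 (5–7%) | 1.01–1.03 (3%) |
| Age, fixed, without age at diagnosis | 1.19–1.20 (15–25%) | 1.33–1.39 (45–55%) |
| Age, time-updated, without age at diagnosis | 2.71 (83%) | 4.78 (100%) |
| Age, time-updated, with age at diagnosis | 3.23 (17%) | 5.83 (23%) |

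Sensitivity checks:

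- *Time off therapy limited to about 15 years, 4-fold rise.* The fixed value with age at diagnosis gave 1.11 per 10 years, significant in 5% of runs.
- *Other hazard form: 0.02 × exp(0.08s), enrollment 3 to 25 years off therapy.* The true ratio is exp(0.8) = 2.23 per 10 years. The fixed covariate averaged 1.00 on the end-of-therapy clock and 1.01 on the age axis, significant in about 5% of runs.
- *Assumed era effect of 0.05 in log hazard per year.* The fixed covariate gave 1.64 to 1.65 per 10 years, significant in 95% of runs. That is the era effect itself, since exp(0.5) = 1.65.

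**Neurocognitive deficits.** These are yes/no results without an onset date. With assessment time used as event time and a true odds ratio of about 1.08 per year, Cox gave a hazard ratio of about 0.28 per year on the age scale. It gave no estimate when the time variable was years off therapy itself. Logistic regression recovered 1.09.

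**The case against.** The strongest reply is that the article never says the covariate is frozen at enrollment. The Part 1 text builds longitudinal data by age interval and treats leukemia diagnosis as time-varying. Years off therapy could be updated in the same way, and such coding is commonly left to an analysis plan that is not shown. This stands in part: the fixed reading cannot be asserted as the text. It remains the natural one, because the article labels leukemia diagnosis as time-varying, gives years off therapy no such label, and lists it among fixed characteristics. The updated reading does not rescue the model either. It is not estimable on an end-of-therapy clock, and with age at diagnosis on the age axis it reached significance in only 17–23% of runs.

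A reader might infer stronger things that the documents do not support:

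- *That the covariate always equals length of follow-up.* This is exact only on an end-of-therapy clock, and the only stated axis is chronologic age.
- *That its hazard ratio is near 1 whatever the truth.* Era or participation effects move it, and so does leaving out age at diagnosis.
- *That every outcome in the sentence is pulled toward 1.* The neurocognitive ratio goes far below 1 or cannot be estimated.
- *That the study's main question is compromised.* The primary aim compares survivors with controls. This is one of six listed factors under a secondary aim, and no aim is framed around the course of risk after treatment.

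**Conclusion.** The point holds for the survivor-only CHC models. With age at diagnosis included, years off therapy at its enrollment value carries essentially no information on whether CHC hazard rises with time off therapy. The near-null result in the simulations follows from the structure, given enrollment timing independent of CHC risk and no era effect. The exact figures depend on the assumed ages, treatment durations and hazard shapes. Because no time origin or coding is stated, the conclusion is conditional on the fixed reading; the time-updated reading fails for a different reason. For the once-assessed neurocognitive deficits, Cox regression is unsuitable. This should be changed before analysis, but it does not affect the primary comparison with controls.

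**What to change.** **CHC models in survivors.** Drop years off therapy fixed at enrollment. Use time since end of therapy as the time scale, and report the CHC hazard by period since therapy (for example 0–5, 5–10 and over 10 years), adjusted for age at diagnosis. State how conditions that began before the end of therapy are handled.

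**If the age axis is kept.** Enter time off therapy only as a time-updated term. State that it is nearly collinear with age at diagnosis, so the two should not both be interpreted in one model.

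**Neurocognitive deficits.** Replace Cox with a cross-sectional model, such as logistic regression, with years off therapy at assessment as an ordinary covariate.

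**Cost.** This is a wording change in the analysis plan. CHC onset dates are already abstracted, and the end of treatment must be known to establish eligibility. The downside is that the effect of time off therapy appears as hazards by period and not as a single adjusted hazard ratio.
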